#### Descriptive analyses at baseline

Descriptive statistics will be presented by intervention group at baseline to investigate the comparability between groups. This will include summary statistics of demographic, stratification, baseline measures of outcomes, and other potential confounding variables.

#### Primary analysis

Descriptive statistics for the WOMAC scale will be presented for each intervention group at 12 months follow-up. We will evaluate the effectiveness of exercise therapy and manual therapy on disability (WOMAC composite score) at 12 months using analysis of covariance (ANCOVA), a form of general linear model [55]. We will include the baseline measure as a covariate in the model, and include adjustment for the stratification variable (condition), and pre-specified potential confounding factors: age, body mass index, baseline pain intensity, duration since first diagnosis, quadriceps muscle strength, mental health, and self-efficacy [56]. These will be included regardless of whether baseline imbalance exists. This approach has been chosen because confounder selection strategies that are based on collected data can result in models with poor statistical properties [57-59]. This will adjust appropriately for any baseline imbalance and will provide the most powerful analysis [57,60]. Adjusted estimates of intervention effect from this model will be reported as the primary analysis in the trial publication.

#### Secondary analyses

Secondary analyses will be undertaken using general linear models to investigate the effectiveness of the interventions for the primary and secondary outcome variables at 9 weeks, 6 months, 12 months and 24 months. We will include the same pre-specified confounding factors as in the primary analysis, the stratification variable, and for continuous outcomes collected at both baseline and follow-up, we will include the baseline measure of the outcome. In addition, estimates of the effectiveness of exercise therapy and manual therapy from models that only include the stratification variable and baseline measure of the outcome will also be presented.

We will report the event rates for joint replacement surgery and the OMERACT-OARSI responder criteria [33,34], and the number needed to treat (NNT) statistics. Logistic regression methods and Cox's proportional hazards model will be used to compare the risk of joint replacement for each of the interventions at 12 month and 24 month follow-up. These models will include adjustment for the stratification variable.

The effect of the interventions over time will be compared using linear mixed models. These models appropriately adjust for correlation that occurs from collecting multiple observations per participant.

Finally, we will investigate (i) if there is an interaction between the two interventions for the primary outcome at 12 months, and (ii) if the effects of the two interventions differ by the condition (hip or knee osteoarthritis). For these analyses we will include appropriate interaction terms in the models [20,21]. The trial is not powered to detect these interactions and is likely to have poor precision for the interaction terms. We plan to report regression coefficients for the interaction terms and their 95% confidence intervals.

No statistical adjustment will be made for multiple testing. All tests will be two-sided and carried out at the 5% level of significance. Changes to the study design or analysis plan will be documented with full justification.

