**Secondary Outcome measures**	

Timed up-and-go	Physical test [38,39]
30 second sit-to-stand	Physical test [37]
40 m self-paced walk	Physical test [32,39]
WOMAC subscales: A) Pain; B) Stiffness C) Physical Function;	WOMAC-3.1 [33,34] patient-rated questionnaire
Numeric pain rating	NPRS [33,34] patient-rated questionnaire
Self-efficacy and pain beliefs	The Pain Belief Screening Instrument [40,41]
Depression	The two-item case-finding instrument [42]
Patient's global assessment	GROC [33,34,36] patient-rated scale
OARSI response criteria	Composite of WOMAC, NPRS, GROC [34]
American College of Rheumatology criteria for diagnosis of OA	Clinician-rated criteria [22-24,45,46] from physical tests and symptoms
New Zealand National Clinical Priority System score	Clinician-rated criteria [47];
Adverse events	MOA field team audit; ODHB records; self-report questionnaire
Overall health status^†^	SF-12 general health survey [43]
Surgical intervention^†^	Self-report questionnaire; health system records [44]
Healthcare consumption and related costs^†^	Self-report questionnaire; health system records

*The primary end-point for data analysis is 12 months. All outcome measures will be undertaken at baseline, 9 weeks, 6 months, 1 year and 2 years, with the exception of patients' global assessment and OARSI response criteria, which will not be assessed at baseline. ^†^The primary endpoint for cost-utility and surgical intervention is at 2 years. WOMAC = Western Ontario and McMaster osteoarthritis index; NPRS = numeric pain rating scale; GROC = global rating of change; OA = Osteoarthritis; OARSI = Osteoarthritis Research Society International; MOA = the Management of OsteoArthritis Trial; ODHB = Otago District Health Board.

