### Participants

We will recruit 224 participants through two sources: a) patients attending general practitioners (GPs) with hip or knee OA; and b) patients attending the Department of Orthopaedic Surgery (Outpatient Clinic, Dunedin Hospital, New Zealand) for an orthopaedic consultation for consideration of hip or knee joint replacement surgery.

To be eligible, participants must meet clinical criteria for diagnosis of OA of the hip or knee according to American College of Rheumatology criteria [22-24].

Exclusion criteria will include:

• previous knee or hip joint replacement surgery of the affected joint;

• any other surgical procedure of the lower limbs in the previous 6 months;

• rheumatoid arthritis;

• initiation of opioid analgesia or cortico-steroid or analgesic injection intervention for hip or knee pain within the previous 30 days;

• uncontrolled hypertension or moderate to high risk for cardiac complications during exercise [25];

• physical impairments unrelated to the hip or knee preventing safe participation in exercise, manual therapy, walking or stationary cycling, such as: vision problems that affect mobility, body weight greater than 155 kg, neurogenic disorder, primary or significantly limiting back pain, advanced osteoporosis, or inability to walk 10 metres without an assistive device;

• inability to comprehend and complete study assessments or comply with study instructions;

• stated inability to attend or complete the proposed course of intervention and follow-up schedule.

Figure 2 shows a diagram illustrating the expected flow of participants through recruitment, assessment and intervention. A research nurse will identify potential participants at the Dunedin Hospital Orthopaedic Clinic point of entry. The research nurse will initially screen each potential participant against the inclusion and exclusion criteria by chart review and questioning by telephone. We will keep a screening log, recording the criteria eliminating all those found to be ineligible. Willing potential participants will be given an appointment at the Centre for Physiotherapy Research, where researchers will obtain informed consent and baseline measures.

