#### Randomisation and allocation concealment

Participants will be randomised using TENALEA, which is an online, central randomisation service, currently in deployment phase with a grant from the e-TEN programme of the European Union (LSHC-CT-510736). This Trans-European Network for Clinical Trial Service provides a secure randomisation service over the internet. The TENALEA service will generate and hold the randomisation schedule. Allocation concealment will be ensured, as the service will not release the randomisation code until the patient has been recruited into the trial, which takes place after all baseline measurements have been completed.

Randomisation will be stratified by condition (hip or knee). Within each stratum, participants will be randomised to one of the four intervention groups using block allocation. The block size will be subject to random variation.

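### The joint-replacement models name only hip or knee as an adjustment; adding recruitment source and baseline WOMAC would be a cheap gain in efficiency for this secondary outcome

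*Protocol article*

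**What the plan says.** In the Protocol article, Secondary analyses, the surgery comparison reads "Logistic regression methods and Cox's proportional hazards model will be used to compare the risk of joint replacement" for each intervention, at 12 and 24 months. The only covariate named is in the next sentence: "These models will include adjustment for the stratification variable". Under Randomisation and allocation concealment, that variable is condition, hip or knee. Recruitment source is not a stratum.

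The preceding paragraph of Secondary analyses says "We will include the same pre-specified confounding factors as in the primary analysis, the stratification variable", but it is about general linear models. The factors it refers to, listed under Primary analysis, are "age, body mass index, baseline pain intensity, duration since first diagnosis, quadriceps muscle strength, mental health, and self-efficacy". Recruitment source is not among them. The baseline measure of the outcome is added only for continuous outcomes measured both at baseline and at follow-up.

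The Participants section names two sources: patients of general practitioners, and hospital clinic patients attending "for an orthopaedic consultation for consideration of hip or knee joint replacement surgery". The Table 1 footnote says "All outcome measures will be undertaken at baseline, 9 weeks, 6 months, 1 year and 2 years", so WOMAC is available at baseline. It also says "The primary endpoint for cost-utility and surgical intervention is at 2 years", while surgery stays in the list of secondary outcomes.

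**The concern.** The clinic group is defined by being considered for the very event that these models analyse, so source is a likely strong predictor of surgery. Baseline WOMAC is another likely one, because the Discussion describes the population as ranging from mild to severe disease. Leaving strong predictors out of a logistic or Cox model lowers the power of the treatment test, and a chance imbalance in source between arms goes uncorrected.

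The choice also departs from the plan's own reasoning. Primary analysis defends pre-specified covariates because they deal with baseline imbalance and give the most power. No reason is given for doing otherwise for surgery, where power is scarcer because the sample size was set for WOMAC alone. In addition, neither the logistic nor the Cox model is named as the main surgery result.

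**Working it through.** **1. The plan's own figures.** None is given for surgery. The WOMAC figures in Sample size reproduce well enough: SE = 50 × √(2/90) = 7.45; half-width 1.96 × 7.45 = 14.6 (stated 14.6); power = Φ(28/7.45 − 1.96) = Φ(1.80) = 96.4% (stated about 95%). They say nothing about power for joint replacement.

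**2. Assumptions.** From the protocol: 224 participants, 112 versus 112 for a main effect, two-sided 5% tests, surgery at 24 months. Everything else is assumed:
- even split by source and by condition; condition OR/HR 1.5
- clinic patients 0.5 SD worse on baseline WOMAC
- surgery rate without the therapy 10, 20 or 30%
- predictor strength (source OR/HR; WOMAC OR/HR per SD): weak (2; 1.5), middle (4; 2), strong (8; 2.5)
- true conditional treatment OR/HR 0.5, one therapy factor modelled, no loss to follow-up

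**3. Power (%), condition only → with source and baseline WOMAC added.** 1,500 simulated trials per logistic cell, 800 per Cox cell; each power carries a Monte Carlo error of about 1 to 2 points.

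| Rate | Predictors | Logistic | Cox |
|---|---|---|---|
| 10% | weak | 21.6 → 22.1 | 24.6 → 27.3 |
| 10% | middle | 22.5 → 23.3 | 22.8 → 24.6 |
| 10% | strong | 21.4 → 24.1 | 21.2 → 25.3 |
| 20% | weak | 43.1 → 45.0 | 47.5 → 49.1 |
| 20% | middle | 36.6 → 40.7 | 42.6 → 52.9 |
| 20% | strong | 31.9 → 40.1 | 37.1 → 49.7 |
| 30% | weak | 53.9 → 56.1 | 61.8 → 68.2 |
| 30% | middle | 45.5 → 51.7 | 56.6 → 69.1 |
| 30% | strong | 36.4 → 45.8 | 50.6 → 73.1 |

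The gain runs from 0.5 (22.1 − 21.6) to 9.4 points (45.8 − 36.4) for logistic and from 1.6 (49.1 − 47.5) to 22.5 points (73.1 − 50.6) for Cox. It is positive in all 18 cells, though the smallest gains are no larger than the simulation error.

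A separate logistic simulation kept both randomised factors in the model (25% rate, source OR 3 to 6, severity OR 1.5 to 1.8 per SD, true OR 0.35 to 0.50). Its gains were 2.5 to 7.5 points, inside the same range.

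**4. Validity.** With no treatment effect (logistic, 20% rate, middle predictors), rejection was 4.6% without and 4.8% with the covariates. The null case was not run for Cox.

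**5. Shift of the estimate.** With condition only, a conditional OR of 0.50 reads 0.51 to 0.60, and a conditional HR of 0.50 reads about 0.50 to 0.58.

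**6. Chance imbalance in source.** With an even split, the SD of the difference in source share between arms is √(0.5 × 0.5 × 2/112) = 0.067. P(difference of 10 points or more) = 2 × [1 − Φ(0.10/0.067)] ≈ 13%. With a 30:70 split the SD is 0.061 and the probability about 10%.

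**7. Cost in events.** Five parameters: two therapy factors, condition, source, WOMAC. At a 25% control rate the odds are 1/3.
- True OR 0.50: treated odds 1/6, risk 14.3%; events 112 × 0.25 + 112 × 0.143 = 28 + 16 = 44; 44/5 = 8.8 per parameter.
- True OR 0.35: treated odds 0.117, risk 10.4%; events 28 + 11.7 = 39.7; 39.7/5 = 7.9.
- At a 10% control rate and OR 0.50 the simulated trials had about 17 to 18 events, or about 3.5 per parameter.

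**The case against.** Adjusting for the variable that stratified the randomisation is a legitimate analysis, and the passage contradicts nothing. A reader might infer that the planned models bias the treatment effect towards no effect. The documents do not support that. The shift in step 5 is mostly non-collapsibility: the condition-only model targets a near-marginal effect, which suits the event rates and numbers needed to treat planned in the same paragraph. The objection stands, and the point is one of efficiency.

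The wording is also open. The sentence says what the models include, not that they include nothing else, and the preceding covariate list might be meant to reach surgery. Its tie to general linear models makes that less likely. On that reading baseline pain, age and disease duration would be in, and the gain would shrink. Recruitment source and baseline WOMAC would still be absent. That model would also have at least ten parameters (two therapies, condition, seven factors), or about 44/10 = 4.4 events each.

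The size rests wholly on assumptions, since the protocol documents no difference in surgery risk between the sources. Power at a true OR of 0.50 stays modest for logistic regression either way (at most 56% in step 3). These limits stand. They bear on how much is gained; the gain was positive in every case simulated.

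**Conclusion.** The point holds as a cheap improvement to a secondary analysis. Two likely predictors of surgery, known at entry, go unused. The planned test remains valid and the WOMAC primary analysis is untouched. For a true OR/HR of 0.5 and a 24-month rate of 10 to 30%, the gain is about 0.5 to 9 points of power for logistic and 2 to 22 for Cox. The upper values need strong predictors and frequent surgery; with few events and weak predictors the gain is close to zero.

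Three further inferences go beyond the documents. The 24-month footnote fixes the time point for surgery and does not make it a primary outcome. Recruitment source is known when a participant enters, but the article does not say that it is stored as a variable. Nothing here shows a need for source in the WOMAC model, which already adjusts for baseline WOMAC and pain.

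**What to change.** Replace the adjustment sentence in Secondary analyses by: *These models will include both randomised factors, condition, recruitment source and baseline WOMAC.* Name the Cox model to 24 months as the main surgery analysis and the logistic models as supportive. Report the condition-only estimates alongside, both as the near-marginal effect and as a safeguard if events are few.

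Make the change before unblinding, which means before the one-year analyses are completed, and document it as the plan requires for changes to the analysis. Confirm that source is entered in the database for every participant.

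The cost is one sentence, no new assessment and two more parameters: about 8 to 9 events per parameter in the 25% case above, fewer if surgery is rarer. A third source category, if community recruitment is opened, would add one more parameter.

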### Economic evaluation

We will assess the incremental costs and the economic consequences of delivering the manual therapy and exercise programmes compared with usual care alone according to established methods for the analysis of patient-level data [61]. We will estimate all health care consumption and costs from a societal perspective using patient self-report questionnaires, and verify hospital admissions from hospital records [62]. We will report incremental cost-utility ratios using quality-adjusted life-years derived from SF-12 scores using appropriate preference weightings [63,64].

Associate [name]	Health economist; advisor to PhD candidate	University of Otago
[name]	Advisor to PhD candidate	University of Otago
[name]	Clinical advisor	Regis University

The principal investigator will instigate and co-ordinate the training of the field team and perform audits of procedures throughout. Off-protocol and adverse event reports will be monitored monthly. Each adverse event will be independently adjudicated by two members of the MOA Trial team, blind to participant group assignment, with a third member to adjudicate in the event of disagreement. Events will be reported to the Data and Safety Monitoring Board.

#### Data and safety monitoring

Data and safety monitoring will initially be referred to the Data and Safety Monitoring Board of the Health Research Council of New Zealand. Should the Board consider the risks low and/or the recruitment period short, they may refer responsibility back to the MOA Trial Team. In this event, we will set up a panel comprising the co-investigators, selected international advisors, and an independent member to which the principal investigator will report regularly.

In the event that more than one serious adverse event of any type or class occurs that was avoidable and related to the physiotherapy programmes, we will suspend the trial. If the cause of the events cannot be determined, reconciled or remediated, we will terminate the relevant arms of the trial.

#### Data quality assurance

To enhance the accuracy of the data we will use optical mark recognition technology (Remark™, Gravic, Inc., Malvern, PA, USA) to transcribe data from paper forms to a spreadsheet, which will input data directly into a relational database (FileMaker Pro™, FileMaker, Inc., Santa Clara, CA, USA) based on a server in the Division of Health Sciences, University of Otago. These methods enable transcription error to be minimised and eliminate the need for manual double entry.

#### Intervention fidelity

Clinician adherence to the intervention protocols will be ensured by collaborative development of the protocols during a 3-day planning and training retreat, protocol-based delivery, a comprehensive MSOP, field training, structured recording forms, monthly field team meetings, audit, observation, feedback, and participant interviews.

#### Publication policy

We will submit the results of the trial for publication in an appropriate journal irrespective of outcome. We will report the trial in accordance with the CONSORT statements [65-67]. The principal investigator will be responsible for timely generation of report manuscripts, and prior to submission the co-investigators will review and approve study results papers arising from the MOA Trial. The principal investigator must approve manuscripts arising from sub-studies nested within the MOA Trial programme. Authorship of manuscripts, presentations and reports related to the MOA Trial programme will comply with the ICMJE "Uniform Requirements for Manuscripts Submitted to Biomedical Journals" [68]. Other significant contributors to the conduct of the MOA Trial will be individually named under the umbrella "the MOA Trial Team" (Table 2).

#### Timetable for the MOA Trial

June 2007 – Grant awarded by the Health Research Council of New Zealand

November 2007 – Ethical approval granted by the Lower South Regional Ethics Committee of the New Zealand Ministry of Health

10 March 2008 – Recruitment starts

March 2009 – Recruitment completed

March 2009 – First participant completes 1-year follow-up

March 2010 – Last participant completes 1-year follow-up

June 2010 – Analysis and publication of 1-year data – re: specific aims 1 & 2. Preliminary report of specific aim 3

March 2011 – Last participant completes 2-year follow-up

June 2011 – Analysis and publication of 2-year data – re: specific aim 3, longer-term report of specific aims 1 & 2.

## Discussion

The MOA Trial will be among the first randomised trials to investigate the effectiveness and cost-utility of manual therapy interventions and/or individually tailored, supervised multi-modal exercise therapy programmes for patients with hip or knee OA. It will respond to the lack of randomised trials to assess long-term outcomes or to include economic analyses. The results will help to establish the best approach to primary care of adults with mild to severe OA of the hip or knee.

## Abbreviations

ACTR: Australian New Zealand Clinical Trials Registry; ANCOVA: analysis of covariance; CRA: Clinical Research Administrator; CONSORT: Consolidated Standards of Reporting Trials; GP: General medical practitioner (family practice physician); HRC: Health Research Council of New Zealand; ICMJE: International Committee of Medical Journal Editors; ITT: intention-to-treat; MOA Trial: Management of OsteoArthritis Trial; MSOP: Manual of Standard Operating Procedures; OA: osteoarthritis; OMERACT-OARSI: Outcome Measures in Rheumatoid Arthritis Clinical Trials – Osteoarthritis Research Society International; SF-12: Short Form twelve item general health questionnaire; TENALEA: Trans European Network for Clinical Trials Services Software for Randomisation in Clinical Trials; WOMAC: Western Ontario and McMaster osteoarthritis index.
